#### INSPIRE adherence monitoring and supervision

We will use methods from our previous studies to assess adherence to session content [54, 55]. A basic checklist will be developed outlining each session’s content. All sessions will be audio recorded and files will be uploaded by facilitators to a secure web server. Session recordings will be reviewed and coded by the INSPIRE trainer and supervisor who will code whether content was discussed and rate the facilitators’ proficiency discussing the content. Weekly phone supervision will also take place where experiences from the prior group are discussed, feedback from recordings provided, and review of next session’s content is outlined and practiced. The intervention will be modified or stopped as determined by the DSMB and IRB if there is clear evidence of harm (e.g., worsening symptoms), a favorable benefit:risk ratio, or an unfavorable risk:benefit ratio. All adverse events will be recorded and communicated to the sponsor, DSMB and IRB per our Data Safety Monitoring Plan protocol. Any modifications to the protocol will be reported to relevant parties including the investigators, participants, sponsor, IRB, and clinicaltrials.gov where the study is registered.

#### Usual care

All patients will be receiving buprenorphine as part of usual procedures in the clinic. Services available for SPs vary by clinic and may include individual behavioral health counseling, psychoeducation groups, and standard primary care services. We will collect information from support persons in UC about the services they received to further quantify this condition.

#### Outcomes

Our primary outcome is patient retention on buprenorphine, measured using data from the EMR, defined as buprenorphine prescriptions of at least 6 and 12 months with no more than a 7-day lapse between prescriptions (see Table 2) [8, 51, 52, 56]. We have two sets of secondary outcomes that correspond to the effectiveness of INSPIRE (specific aim 1). For the patient, we will validate adherence using urine test results in the EMR for buprenorphine metabolites, and will assess, through patient self-report, patient opioid and other substance use in the past month, overdose risk, substance use problems, health, other employment, quality of life, communication, employment, and treatment satisfaction. For the SP, our secondary outcomes are self-reported and will include the SP’s physical and mental health (depression and anxiety), substance use, quality of life, and relationship quality with their person. These outcomes have been validated with high psychometric properties in existing CRAFT trials [8, 19–24]. Self-report will be assessed via in-person interview during baseline, and phone-based interviews at 3- and 12-month follow-ups. RAND staff who conduct interviews will be masked to condition.

**Table 2 Tab2:** Outcome measures

Source	Timepoint	Outcome	Description
Primary outcome measures			
EMR	6, 12	Buprenorphine retention	Percentage of patients who initiated buprenorphine who have at least 6 and 12 months of continuous treatment with buprenorphine with no more than a 7-day lapse between prescriptions [51, 52] Number of days of longest continuous buprenorphine treatment with no breaks in care

Source		Outcome	Description
Secondary patient outcome measures			
P INT SP INT	BL, 3, 12 BL, 3, 12	Patient opioid use	Heroin, prescription opioid, and other opioid use in the past 30 days using questions from the National Survey on Drug Use and Health [57–59]
EMR	6, 12	Medication adherence	Percentage of patients with a buprenorphine prescription with a urine test positive for buprenorphine metabolites
EMR	6, 12	OUD treatment retention	Percentage of patients who initiated OBOT who had continued visits (no more than a 30-day lapse between visits) with any provider for a substance use disorder for 3, 6, and 12 months [8, 56]
P INT SP INT	BL, 3, 12 BL, 3, 12	Patient other substance use	Alcohol and other drug use in the past 30 days [58, 59]
P INT	BL, 3, 12	Overdose risk	Opioid Overdose Risk Assessment scale [60]
P INT	BL, 3, 12	Patient Substance use problems	Substance-related problems in the past 30 days using the Short Inventory of Problems
P INT	BL, 3, 12	Patient health	Physical health in the past 30 days; depression and anxiety
P INT	BL, 3, 12	Quality of life	Functional impairment in work/school, family, and social life using the 5-item Sheehan Disability Scale [61]
P INT	BL, 3, 12	Communication	Adapted from the FACES IV [62]
P INT	BL, 3, 12	Employment status	Full-time, part-time, unemployed, other (e.g., students, persons keeping house or caring for children full time, retired or disabled persons) [63]
EMR P INT	6, 12 BL, 3, 12	Healthcare utilization	Number of outpatient medical and behavioral health visits over the 12-month period
P INT	3, 12	Treatment satisfaction	Client Satisfaction Questionnaire (CSQ-8) [64]
Secondary SP outcome measures			
SP INT	BL, 3, 12	Health	Physical health in the past 30 days; depression and anxiety
SP INT	BL, 3, 12	Substance use	Alcohol and other drug use in the past 30 days [58, 59]
SP INT	BL, 3, 12	Quality of life	Functional impairment in work/school, family, and social life using the 5-item Sheehan Disability Scale [61]
SP INT	BL, 3, 12	Communication	Adapted from the FACES IV [62]
SP INT	3	INSPIRE satisfaction	Client Satisfaction Questionnaire (CSQ-8) adapted to INSPIRE [64]

BL: baseline; 3: 3-month follow-up; 6: 6-month; 12: 12-month follow-up; EMR: electronic medical record; P INT: patient interview; SP INT: support person interview; FACES IV: Family Adaptability and Cohesion Scale IV; OBOT: office-based opioid treatment

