### Participants

In Phase 1, eligible participants will be patients 18 or older who are currently receiving buprenorphine and nominated to participate by one of their buprenorphine treatment providers. Eligible SPs will be 18 or older nominated by patients to participate. In Phase 2, staff will include all medical staff who interface with patients in buprenorphine treatment. In Phase 3, eligible study participants will be patients 18 or older who: [1] have completed at least one medication evaluation visit; [2] have no medical contra-indications to buprenorphine, as determined by the patient’s provider; and [3] have an eligible SP they are willing to have participate. Patients who are new to buprenorphine (defined as [1] not receiving a buprenorphine prescription from the study clinic in the past 90 days and [2] patients who return to buprenorphine, defined as not taking buprenorphine for seven or more days in the past 30 days) will be screened. Eligible SPs are those who are: [1] 18 or older; [2] in frequent contact with their person (three times a week or more); [3] not concerned they would be physically hurt by their person; [4] willing and available to attend sessions to address issues related to opioid use by their person if assigned to INSPIRE; [5] committed to their relationship in the next 90 days (no plans to move or end the relationship), and [6] do not currently have a problem with heroin or pain pills [21, 23]. To enroll, the patient’s SP must consent within 1 month of patient consent; this timing was determined based on feedback from providers that some SPs are reluctant to be a part of the patient’s recovery until they see them start buprenorphine. Patients and SPs must both consent for the dyad to be enrolled. According to data from the 12 CHCs, on average patients on buprenorphine were about 51% male; 62% White, 18.2% Multi-race, 13% Black/African American, 3.7% Asian/Pacific Islander, and 2.7% American Indian/Alaskan Native. Research staff will consent individuals.

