**Fig. 2 Fig2:**

Study flow

RAND will contact the patient and describe the study in more detail. A RAND study team member will meet patients in person at the clinic, however, if in-person contact is not feasible, this procedure could occur by phone. RAND staff will ask patients for permission to contact their SP. The goal would be to identify SPs who have a significant impact on their life [50]. RAND will recruit the patient at their first or second visit with the medical provider as some patients may be in withdrawal at their first visit. SPs will be recruited within a month of the patient’s consent.

Once enrolled in the study, patients and SPs will be interviewed separately at all time points (baseline, 3, 12 months). Participants will receive a $5 incentive for screening, $30 for the baseline interview survey, $30 for the 3-month interview and $40 for the 12-month interview. In addition, SPs assigned to INSPIRE may receive transportation and/or childcare remuneration to attend sessions as needed. All participants and SPs will be contacted for follow-up, regardless of whether they complete INSPIRE or UC, and we will conduct intent-to-treat analyses. A total of 770 dyads are expected to consent to the study, resulting in a total of 616 dyads at 3-month follow-up (assuming 80% retention) and 500 dyads at 12-month follow-up (assuming 65% retention) (see Fig. 3). To ensure robust follow-up rates, we will obtain detailed information at baseline on how to reach participants and use proven methods to minimize attrition, including an in-person baseline interview to build rapport, obtaining multiple contacts (friends/families/service providers) at baseline for individuals who would know the participants’ whereabouts, and phone/mail/text/social media reminders prior to follow-up.

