**Fig. 3 Fig3:**
[figure not shown]
Study flow

We will examine patient electronic medical records (EMRs) to assess buprenorphine medication retention (i.e., no more than a 7-day lapse between prescriptions) [51, 52], healthcare utilization (e.g., number of medical and behavioral health visits), and results of urine tests (e.g., presence of buprenorphine and other opioids). All data will be stored on encrypted laptops used only for research purposes that require staff to login and provide a personal password to access. Files that have personally identified health information will also be password protected.

Randomization will conducted by research staff at the dyad-level such that patients and SPs both need to consent to be randomized. Dyads will be stratified by clinic and by SP type. We will stratify participating SPs who are patients’ parents equally to INSPIRE or UC because of existing CRAFT studies showing a stronger effect of CRAFT for parents [8] using permuted block randomization with random size blocks. This ensures the number of people allocated to each group is approximately equal throughout recruitment [53]. Data collectors will not be blind to SP intervention condition because they will need to schedule SPs for the INSPIRE class, but are independent and not part of the core research team. In addition, to minimize bias, they will emphasize to participants that their responses would be confidential and not conveyed to the clinics, will conduct follow-up interviews outside of the clinic, and will build rapport with participants to increase self-report validity.

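### Table 2 takes urine-confirmed adherence only among patients with a prescription, a group that retention itself shapes, so the planned comparison between arms is not as randomised

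*Protocol article*

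**What the plan says.** **Adherence.** Outcomes, Table 2, lists medication adherence as a secondary patient outcome, taken from the medical record at 6 and 12 months: "Percentage of patients with a buprenorphine prescription with a urine test positive for buprenorphine metabolites". The text above the table ties the secondary outcomes to the effectiveness aim, and the Phase 3 analysis plan compares primary and secondary outcomes between INSPIRE and usual care with mixed models.

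**Retention.** Table 2 gives the primary outcome as "Percentage of patients who initiated buprenorphine who have at least 6 and 12 months of continuous treatment" and OUD treatment retention as "Percentage of patients who initiated OBOT who had continued visits". The paragraph above the table defines primary retention without any restriction to initiators.

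**Analysis principle.** The Phase 3 text after Fig. 2 says that everyone is followed up "regardless of whether they complete INSPIRE or UC, and we will conduct intent-to-treat analyses".

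**Order of events.** Under Participants, patients must "have completed at least one medication evaluation visit"; a first dose or prescription is not required. Randomisation is "at the dyad-level such that patients and SPs both need to consent to be randomized", and "the patient’s SP must consent within 1 month of patient consent".

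**The concern.** A percentage compares the arms as randomised only if its denominator was fixed before randomisation or cannot be changed by treatment. Whether a patient holds a prescription at 6 or 12 months is neither. It is close to the primary outcome. If INSPIRE keeps more patients on buprenorphine, its adherence denominator grows by the very patients whom usual care would have lost. The two percentages then describe different kinds of patient. The conditional percentage also gives no credit for keeping those patients in treatment. Adjusting for baseline covariates, as the analysis plan intends, does not in general remove selection on something that happens after randomisation.

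The same question arises for the retention percentages if a patient can be randomised and then never start. Leaving that patient out removes a failure, and if starting differed between arms the removal would be unequal.

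**Working it through.** **The plan's own figure.** Phase 3 sample size and power states 80% power for 51% v 65% with 250 dyads per arm and two-sided alpha 0.05/2. With z = 2.241 and 0.842 and mean proportion 0.58:

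n = [2.241 × √(2 × 0.58 × 0.42) + 0.842 × √(0.51 × 0.49 + 0.65 × 0.35)]² / 0.14² = 235 per arm

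With continuity correction this becomes 250, which matches. Without the correction, power at 250 is 82.6%. The figure is not in dispute, and it deducts nothing for non-initiators.

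**Adherence denominators.** Taking prescription holding at 12 months as equal to retention, the denominators are 0.51 × 250 = 127.5 and 0.65 × 250 = 162.5, about 128 v 163.

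**Effect on the adherence comparison.** The protocol article gives no urine-positivity rate, so two are assumed:
- a: positivity in the 51% who would be retained in either arm;
- b: positivity in the further 14% retained only because of INSPIRE.

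The formulas are:
- among prescription holders: usual care a; INSPIRE (0.51a + 0.14b)/0.65; difference (0.14/0.65)(b − a);
- among all randomised, with no prescription counted as not adherent: usual care 0.51a; INSPIRE 0.51a + 0.14b; difference 0.14b.

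Example with a = 90% and b = 60%:
- holders: (0.459 + 0.084)/0.65 = 83.5% v 90.0%, a difference of -6.5 points;
- all randomised: 54.3% v 45.9%, a difference of +8.4 points.

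| a | b | Difference, holders (points) | Difference, all randomised (points) |
|---|---|---|---|
| 95% | 90% | -1.1 | +12.6 |
| 95% | 40% | -11.8 | +5.6 |
| 90% | 90% | 0 | +12.6 |
| 90% | 60% | -6.5 | +8.4 |
| 80% | 80% | 0 | +11.2 |
| 80% | 40% | -8.6 | +5.6 |

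Over a = 80-95% and b = 40-90%, with b no higher than a, the holders' difference runs from 0 to -11.8 points and the all-randomised difference from +5.6 to +12.6. If b exceeded a, the holders' difference would be positive.

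**Initiator denominators.** Hold retention among all randomised at 51% v 65% and divide by the assumed share initiating:

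| Initiating, usual care / INSPIRE | Usual care | INSPIRE | Difference (points) |
|---|---|---|---|
| 100% / 100% | 51.0% | 65.0% | 14.0 |
| 90% / 90% | 56.7% | 72.2% | 15.6 |
| 90% / 95% | 56.7% | 68.4% | 11.8 |
| 85% / 95% | 60.0% | 68.4% | 8.4 |

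If everyone starts before randomisation, nothing changes. Equal later initiation rescales both arms, and unequal later initiation distorts the contrast.

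**The case against.** **Adherence as a validity check.** The Outcomes text says urine results serve to validate adherence, and for that purpose conditioning on a prescription is natural. This stands as a reason to keep the percentage as a description. It does not answer the point, because the measure is also listed as a secondary effectiveness outcome to be compared between arms.

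**The word prescription.** Table 2 does not say whether it means a current prescription or any prescription. If any, the denominator is close to everyone who started, and little remains beyond the initiation question. The 6- and 12-month timepoints favour a current one. Even then, holding a prescription is not the same as being retained: a patient who lapsed for more than 7 days and restarted holds one but fails the primary outcome. The 128 v 163 is therefore an approximation.

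**Intent to treat.** The statement speaks of completing the assigned condition, and Table 2 describes measures rather than analysis sets. It is fair to say that the denominators do not fit the principle, not that the article flatly contradicts itself.

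**Initiation.** A reader might infer that the initiator restriction is a post-randomisation exclusion from the primary outcome. The text does not establish this. Overview of study procedures has patients screened as they begin or resume buprenorphine. Participants explains the one-month window by support persons who hold back until the patient has started. Usual care says that all patients will be on buprenorphine. Most will probably have started before the dyad is randomised, and for them the restriction is harmless. What remains is that the evaluation-visit criterion, with recruitment at the first or second visit, leaves a randomised never-starter possible, and that Table 2 and the paragraph above it word the primary denominator differently.

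**Conclusion.** The point holds for the secondary adherence percentage, provided that prescription means a current one. Its denominator is affected by treatment, and the planned comparison between arms is not a randomised comparison.

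A reader might infer that adherence will look worse because INSPIRE works. The documents do not support that. It requires the additionally retained patients to test positive less often than the others, and no figure in the article says so; with equal rates the conditional difference is 0. The ranges of 0 to about -12 points (holders) and about +6 to +13 points (all randomised) rest on the planning rates of 51% v 65%, the assumed positivity rates, prescription holding standing in for retention, INSPIRE losing no one whom usual care would keep, INSPIRE not changing positivity in those retained either way, and no missing tests.

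For the two retention percentages the point is conditional and smaller: it matters only if some patients are randomised before they start.

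Nor does it reach every outcome from the medical record. Healthcare utilization and days of longest continuous treatment do not use the prescription-holder denominator.

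**What to change.** In Table 2:

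1. Make all randomised patients the denominator of both retention percentages, and count a patient who never starts as not retained. Align the paragraph above the table with this.
2. For the adherence comparison between arms, define a yes/no outcome for every randomised patient: active prescription and buprenorphine-positive urine at the timepoint. State what counts as active, how a missing urine test is handled, and a sensitivity analysis for missing tests.
3. Keep the percentage positive among prescription holders, labelled as descriptive and without a test between arms.

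The cost is a change of wording. The data are the same and the 250-per-arm calculation is unaffected. The percentages will be lower. The composite partly overlaps with retention and so no longer isolates adherence, which is why the descriptive percentage is worth keeping. Its result will also depend on how often urine is tested, which may follow visit attendance; the sensitivity analysis is there for that reason.

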##### Phase 3 sample size and power

We focus our power calculations for the pre-specified comparative effectiveness analyses on the primary outcome of retention at 12 months, for which we will have 250 dyads per condition (N = 500 dyads total). Based on literature, we assume 51% of patients in OBOT will be retained in treatment [65]. We would have 80% power (alpha = 0.05/2, two-sided, two-sample test) to detect a difference of 51% versus 65% between OBOT and CRAFT + OBOT. Our ability to detect this effect is plausible, considering Roozen et al. [23] reported an even larger difference of 30% versus 64% in a systematic review of CRAFT for substance abuse treatment. Given this primary statistical test and the pre-specified heterogeneity of treatment effect (HTE) analysis examining retention described below, we adjust for multiple comparisons by using an alpha level of 0.05/2. To further account for multiple statistical testing given that we will also conduct secondary analyses, we will compute and report false discovery rates [66].

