## Specific aims and hypotheses

The Specific Aims of this project are to: [1] assess the effectiveness of INSPIRE compared to usual care (UC) on buprenorphine retention (primary outcome); [2] examine which patient sub-populations (e.g. addiction severity, race/ethnicity, SP relationship type—e.g., parents, spouse) benefit most from SP involvement in INSPIRE; and [3] assess the patient, provider, and clinic-level factors thought to influence implementation, effectiveness, and sustainability of buprenorphine and INSPIRE. We hypothesize that patients with SPs participating in INSPIRE will have greater buprenorphine retention than patients whose SPs are not participating in INSPIRE, and, consistent with existing CRAFT trials, SPs will experience improved health and quality of life [19–29].

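### The fixed 0.05/2 split between the primary retention test and the heterogeneity analysis is valid, but recycling the alpha (Holm) would add power, mainly for the heterogeneity aim, at the same family-wise 0.05

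*Protocol article*

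**What the plan says.** All of this stands in the protocol article, mostly under Phase 3 sample size and power.

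- The power calculation concerns "the primary outcome of retention at 12 months", "for which we will have 250 dyads per condition (N = 500 dyads total".
- The control rate is an assumption: "we assume 51% of patients in OBOT will be retained in treatment". The target is "to detect a difference of 51% versus 65% between OBOT and CRAFT + OBOT".
- The level is already the reduced one: "We would have 80% power (alpha = 0.05/2, two-sided, two-sample test".
- The reason for halving is given as two items: "Given this primary statistical test and the pre-specified heterogeneity of treatment effect (HTE) analysis examining retention described below". The rule follows: "we adjust for multiple comparisons by using an alpha level of 0.05/2".
- Under Specific aims and hypotheses, the second aim is to "examine which patient sub-populations" benefit most. Addiction severity, race/ethnicity and type of support person are given as examples of moderators.

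False discovery rates are promised in connection with the secondary analyses. The article states no ordering, step-down or recycling of alpha between the primary test and the HTE analysis.

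**The concern.** As written, each of the two items is judged at 0.025 and a success on one does nothing for the other. Two examples show what this costs.

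- Primary p = 0.001, HTE p = 0.04: the HTE result cannot be claimed under the fixed split. Under Holm it can.
- Primary p = 0.03, HTE p = 0.01: the primary fails under the fixed split and succeeds under Holm.

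The family-wise error bound is 0.05 under both rules, so the fixed split gives up these rejections without buying better error control. The HTE aim has most to lose. The article states power only for the primary comparison, and the primary is likely to succeed if the design assumptions are right, so its alpha would usually be free to pass on. The randomisation is stratified on parent v other support person because a stronger effect in parents is expected, so at least one moderator is of real interest.

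**Working it through.** **Inputs from the article.** n = 250 per arm; p1 = 0.51; p2 = 0.65; two-sided 0.025; stated power 80%.

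**1. Reproduce the stated power.** Mean rate 0.58.
- Standard error under the null: √(2 × 0.58 × 0.42 / 250) = 0.04415.
- Standard error under the alternative: √((0.51 × 0.49 + 0.65 × 0.35) / 250) = 0.04370.
- z for two-sided 0.025 = 2.2414; for two-sided 0.05 = 1.9600.
- With continuity correction (difference less 1/n = 0.140 − 0.004 = 0.136): power at 0.025 = Φ[(0.136 − 2.2414 × 0.04415) / 0.04370] = Φ(0.848) = 80.2%. The sample size for 80% is exactly 250 per arm.
- Without the correction: Φ(0.939) = 82.6%.

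The stated 80% is therefore reproduced. Reading 0.05/2 as one tail of a two-sided 0.05 test would need only 208 per arm (corrected), which does not match. The alpha really is halved.

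**2. Power of the primary at the full 0.05.** Corrected: Φ[(0.136 − 1.9600 × 0.04415) / 0.04370] = Φ(1.132) = 87.1%. Uncorrected: 88.9%. The increments over 0.025 are 6.9 and 6.3 points.

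**3. Error control under Holm.** If both null hypotheses are true, a false rejection requires the smaller p-value to be at most 0.025, which has probability at most 0.025 + 0.025 = 0.05. If only one is true, it is tested at 0.05 at most. Independence is not needed. With independent tests and both nulls true, both rules give 1 − 0.975² = 0.0494.

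**4. Gain in power.** Assumptions, not in the article: one HTE test, independent of the primary, with power q at 0.025. For a normal test statistic, q = 20%, 30%, 50% at 0.025 corresponds to q′ = 28.8%, 40.4%, 61.1% at 0.05.
- HTE under Holm = q + P × (q′ − q), where P is primary power at 0.025.
- Primary under Holm = P + q × (increment from step 2).

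| HTE power, fixed split | HTE, Holm (corrected P = 80.2%) | Primary, Holm (corrected) | HTE, Holm (uncorrected P = 82.6%) | Primary, Holm (uncorrected) |
|---|---|---|---|---|
| 20% | 27.0% | 81.6% | 27.2% | 83.9% |
| 30% | 38.3% | 82.3% | 38.6% | 84.5% |
| 50% | 58.9% | 83.6% | 59.2% | 85.8% |

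The HTE analysis gains about 7 to 9 points and the primary about 1 to 3, with or without the continuity correction.

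**5. If the HTE analysis is several tests.** Plain Holm over the primary and the three moderators named as examples would start at 0.05/4 = 0.0125. Primary power at that first step is 72.2% corrected, against 80.2% now. The recycling must therefore run between the two aims, with the moderator tests kept together as one family on their own share.

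**The case against.** The strongest reply is that nothing here is wrong. Bonferroni is a valid correction, the power calculation already uses it, and the target is met. That stands in full. A reader might infer that the plan is in error or the trial underpowered, and the article does not support this.

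A reader might also compare 82.6% with 88.9% and conclude that the split costs the primary about 6 points. Under Holm, 88.9% is a ceiling, reached only if the HTE analysis always succeeds at 0.025. Interaction tests rarely have such power.

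Other replies stand in part.
- **The unseen analysis plan.** The value 0.025 is also Holm's first threshold, so the sample size would be the same under a step-down rule. A statistical analysis plan may already contain one, in which case the point is met. The rule that the article itself states is the fixed split.
- **The number of HTE tests is unknown.** Moderators are listed only as examples. This limits the form of the fix (step 5) but does not remove the gain.
- **A single joint interaction test.** It might seem a necessary part of the change. It is not, and it would not by itself answer which sub-populations benefit.
- **A self-contained primary.** Under the fixed split the primary is judged alone, with a matching 97.5% interval. Under Holm a primary p-value between 0.025 and 0.05 counts only if the HTE analysis succeeds. Preferring the former is legitimate, but it is no argument against passing alpha from the primary to the HTE analysis.

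**Conclusion.** The point holds as a cheap improvement in efficiency. The fixed split controls the error and delivers its stated power, but a step-down rule is never worse for decisions at the same family-wise 0.05. That dominance needs no assumption about power or dependence. The size does: about 7 to 9 points for the HTE aim and about 1 to 3 for the primary rest on one HTE test, independent of the primary, with 20% to 50% power at 0.025. The article gives no figure for any of these. Priority is low.

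**What to change.** Before unblinded outcome data are seen, replace the fixed split by a statement of this kind:

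*The primary 12-month retention test and the HTE analysis are each assessed at two-sided 0.025. If the primary test is significant at 0.025, the HTE analysis is assessed at 0.05. If all HTE hypotheses are rejected at 0.025, the primary test is assessed at 0.05. Where the HTE analysis comprises several moderator tests, they form one family and share the HTE alpha.*

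A single joint interaction test is optional. If the team wants the primary conclusion to stand on its own, it can drop the third sentence. The HTE gain is then unchanged, and only the 1 to 3 points for the primary are given up.

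The cost is a few lines of text. The sample size and the power statement stay as they are. Confidence intervals will not correspond one-to-one to the step-down decisions, so the report should say which level its intervals use.
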